#### Statistical analysis

The intention-to-treat approach is utilized to examine differences in the fistula closure time among the three groups in the primary analysis by the Pearson χ2 test. Safety parameters and secondary efficacy parameters will be analyzed using the Pearson χ2 test and logistic regression (if necessary). Cox proportional hazards models and the Kaplan-Meier method will also be applied. Adverse events will be tabulated according to randomized group assignment and the proportions will be compared using Fisher’s exact test.

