## Background

An enterocutaneous fistula (ECF) still remains as one of the most complex and challenging complications encountered in surgical practice [1]. Its management often requires a costly hospital stay and multidisciplinary care due to high morbidity and mortality induced by sepsis, hemorrhage, malnutrition and electrolyte disturbances [2, 3]. Staged fistula treatment involves recognition and stabilization, anatomic definitioxn and decision, and definitive operation. With sufficient time, conservative treatment can result in spontaneous fistula closure, with rates varying from 15 % to 71 % [4]. However, this also results in long-term discomfort.

Use of fibrin glue (FG) in the fistula tract has been shown to promote closure of low-output ECFs. As a noninvasive option, it could avoid the risk of developing further dehiscence compared to surgical operations. The application of glue has been reported in recent years for intestinal fistula in case reports [5, 6] and small series [7–10]. Commercial fibrin sealants are usually made from porcine/bovine blood products, whereas autologous adhesives have potential advantages, such as a low risk of infection transmission [11] and provision of a matrix for tissue regeneration [12]. Both are used in clinical practice, but they have not yet been compared to fistula sealing.

Our previous study demonstrated that autologous platelet-rich fibrin glue (PRFG) treatment significantly decreased time the time to fistula closure and promoted closure rates. During the follow-up, no treatment-related adverse events or severe adverse events were observed [13]. The previous study was a prospective, nonrandomized single-center study. There were several limitations in the nonrandomized study, which may have led to bias in our conclusion. Thus, a multicenter, randomized, controlled clinical trial is designed to evaluate the glue application in the treatment of patients with low-output volume ECFs.

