### Objectives

The objective of this study was to investigate the efficacy and safety of glue sealing (using PRFG or the commercially available fibrin sealant Yueling™) in the management of patients with low-output ECFs.

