### Trial design

The trial is designed as a multicenter, open-label, randomized, controlled trial with three parallel groups (two treatment groups and one control group) and a primary endpoint of fistula closure time during the 14-day treatment period. The randomization will be performed by Internet-based software with a 1:1:1 allocation. No blinding will take place in this study.

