#### Interventions

Qualified subjects will randomly be assigned to one of three study groups: two treatment groups offered autologous PRFG (Group A) or commercial porcine fibrin sealants (Group B) and one control group with drainage cessation (Group C).

All groups receive standard of care (SOC) before assessment for inclusion. The SOC comprises supportive measures to stabilize the fistula patient, including fluid/electrolyte balance, bowel rest, nutritional replacement, wound care, and antibacterial therapy in patients with signs of systemic sepsis or inflammation with pain. Nasogastric or nasointestinal feeding will be provided whenever possible; otherwise, parenteral nutrition along with 0.9 g/24 h somatostatin (Stilamin, Serono, Switzerland) will be infused intravenously. To assist in remission of infection, normal saline will be dripped continuously to rinse the fistula tracts; at the same time, percutaneous suction drainage of these tracts is conducted. Nursing staff monitor the daily external output by collecting output volumes. Once the daily fistula volumes decrease to 200 ml, the patients will be evaluated by the coordinating center.

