#### Sample size

The sample size is to be calculated based on detecting the minimal, clinically relevant difference in the success rates of the three arms. Our preliminary study, which enrolled 145 patients, compared the efficacy of PRFG application (PRFG group) with drainage cessation (control group) when low output volume was achieved (<200 ml/d). During the 28-day treatment period, 77 % (58/75) of the patients in the PRFG group experienced fistula closure in comparison to 57 % (40/70) in the control group (*P* = 0.0127) [13]. The unpublished data of the pilot study demonstrated that closure rates were 80 % (60/75) in the PRFG group and 50 % (35/70) in the control group during the 14-day observation period. Due to the above raw data, the closure rates in the two treatment groups and one control group are assumed to be 80 % and 50 %, respectively. In this way, 51 patients per group are needed for this trial based on an alpha of 0.05, with a power of 90 %. Taking into account a drop-out rate of 10 %, a total sample size of 171 patients would be included, with 57 participants in each group.

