## Discussion

To our knowledge, this is the first study to evaluate the safety and efficacy of both autologous and commercial fibrin glue sealing for patients with low-output fistulas. Currently, fibrin glue is indicated only in treating simple ECFs of low-output volume as a first line therapeutic option. Therefore, complex or high-output ECFs are excluded from this study. In addition, this study is designed as an open-label, three-arm study, with autologous and commercial fibrin glue in two treatment groups and drainage cessation for use as a placebo. Because the autologous fibrin sealants require blood donation from patients themselves, patient blinding cannot be conducted. Further, there is a possibility that spontaneous closure can be achieved for fistula patients. Therefore, the control group is being established for comparison of the efficacy and safety of the glue application. In this way, this study is designed as an open-label and three-arm study.

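### The stated primary test asks only whether the three groups differ, while the objective and the sample size concern glue versus drainage cessation, so a significant result does not say which glue works

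*Protocol article*

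**What the plan says.** The trial randomizes 1:1:1 to "two treatment groups offered autologous PRFG (Group A) or commercial porcine fibrin sealants (Group B) and one control group with drainage cessation (Group C").

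- **Objectives:** the aim is to "investigate the efficacy and safety of glue sealing (using PRFG or the commercially available fibrin sealant Yueling™") in low-output fistulas.
- **Discussion:** because fistulas can close spontaneously, "the control group is being established for comparison of the efficacy and safety of the glue application".
- **Background:** on the two glues it remarks, "Both are used in clinical practice, but they have not yet been compared to fistula sealing".
- **Sample size:** "the closure rates in the two treatment groups and one control group are assumed to be 80 % and 50 %, respectively". With alpha 0.05 and 90% power this gives 51 per group, then 57 per group and 171 in total after 10% drop-out.
- **Statistical analysis:** the one primary analysis is to "examine differences in the fistula closure time among the three groups in the primary analysis by the Pearson χ2 test". The section adds that "Cox proportional hazards models and the Kaplan-Meier method will also be applied", without tying these methods to a comparison. It names neither a pair of groups nor a rule for moving from the three-group result to a statement about one product.

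**The concern.** Two products are on trial, and the reader will want a verdict on each. A test of any difference among three groups has no direction and no named pair. If it rejects, the supported conclusion is that the three arms are not all alike. It can reject because both glues work, because only one does, or because the glues differ from each other.

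The sample size section plans for something else: a glue arm against the control arm. The power statement and the primary test therefore refer to different hypotheses.

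At stake is an efficacy claim for PRFG or for the porcine sealant that the primary result does not carry. If pairwise tests are then run with no stated rule, the error rate of the product claims exceeds 5%. The trial is open-label, so the choice of follow-up comparison should be fixed in writing. This point is separate from the use of a chi-square test for a time outcome: it would remain under a three-group log-rank test.

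**Working it through.** **Inputs.** From Sample size: 80% closure in each glue arm (A, B), 50% in control (C), alpha 0.05, power 90%, 51 per group, 10% drop-out. From Statistical analysis: a Pearson chi-square across three groups. Assumptions: two-sided testing (sidedness is not stated), and the primary read as closed or not closed by day 14, because a Pearson test needs categories.

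**1. The plan's own figure.** Two-group formula with pooled variance under the null and mean rate 0.65:

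n = [1.960·√(2·0.65·0.35) + 1.2816·√(0.8·0.2 + 0.5·0.5)]² / 0.30²
= [1.960·0.6745 + 1.2816·0.6403]² / 0.09
= (1.3221 + 0.8206)² / 0.09 = 4.591 / 0.09 = 51.01

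This matches 51. A one-sided test would give 42. Drop-out: 51/0.90 = 56.7, so 57; 3 × 57 = 171. All three stated figures reproduce, and the sizing is that of one glue arm against control.

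**2. What the three-group test would need.** Noncentrality per patient per arm = Σ(pᵢ − p̄)² / [p̄(1 − p̄)]. At 80/80/50, p̄ = 0.70, so (0.01 + 0.01 + 0.04)/0.21 = 0.2857. A 2-df test at 0.05 with 90% power needs noncentrality 12.65, and 12.65/0.2857 = 44.3, so 45 per group. The sample size section therefore did not size the test that the analysis section names.

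**3. Operating characteristics at 51 per arm.** Uncorrected Pearson tests, two-sided 0.05, exact enumeration of the three binomials. Superior means significant in the glue's favour. Rates are A/B/C.

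| True rates | Three-group test positive | A superior to C | B superior to C | Both superior | Three-group positive, exactly one glue superior |
|---|---|---|---|---|---|
| 80/80/50 | 93.5% | 90.3% | 90.3% | 83.8% | 9.8% |
| 80/65/50 | 83.7% | 90.3% | 35.6% | 35.0% | 48.5% |
| 80/50/50 | 92.7% | 90.3% | 3.0% | 3.0% | 84.8% |

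Only the first row is the plan's assumption. The other two are illustrations in which the porcine sealant is weaker or has no effect. The first and last rows show the point: the primary test is positive about equally often whether both glues work or one does.

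**4. One table of results at 57 per arm.** Closures 46/29/29 (80.7%, 50.9%, 50.9%): three-group p = 0.0008, A vs C p = 0.0008, B vs C p = 1.0. The primary test is clearly significant, yet nothing supports B.

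**5. Error rate of follow-up tests under 50/50/50, 51 per arm.**

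- A vs C and B vs C, each at 0.05, no gate: at least one significant in 10.7% of trials (9.2% under 65/65/65).
- The same two tests, run only if the three-group test is significant: 4.1%.

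These count differences in either direction. Counting only results that favour a glue, they are 5.3% and 2.1%.

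**6. Power with the gate at 80/80/50, 51 per arm.** One named glue vs control 88.6%; both glues 83.7%.

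**7. Precision of A vs B at 80% each.** Half-width of the 95% CI = 1.96·√(2·0.8·0.2/51) = 0.155, about ±15.5 percentage points (±14.7 at 57 per arm).

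**The case against.** The strongest reply is that this is detail for an analysis plan that is not shown. The article summarizes its analysis in a few sentences, does not exclude pairwise follow-up, and mentions Cox models that could supply glue-versus-control estimates. The remedy even keeps the three-group test. Part of this stands: no one can say from this document that the follow-up will be chosen after the data are seen. But the document does more than leave a gap. It fixes a primary test that differs both from its objective and from the comparison it sized, and the Cox models are tied to no comparison.

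A second reply is that the intent is plain from the assumed 80% and 50%. Those rates do point to glue versus control. They fit A vs C, B vs C and pooled glue vs C alike, so they do not settle which one decides.

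A third reply is that the size is adequate for either reading: 93% power for the three-group test and 90% for one glue vs control. That is right. The sample size is not wrong, and the 84% for both glues matters only if both must succeed, which the document does not require.

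A reader might also infer that the possible comparisons give opposite verdicts on the same data. The document does not support that. It fixes the three-group test as the deciding one. Where that test is not significant, there is no primary claim, whatever a pairwise or pooled p-value shows. Where it is significant, differing pairwise results answer different questions. At the planned rates, the three-group and pooled tests disagree in only about 3.6% of trials. Nor do the planned rates support a scenario in which a glue does worse than control.

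**Conclusion.** The concern holds as a mismatch between the primary test and both the objective and the sizing. A significant primary result does not say which glue works: it is expected in about 93% of trials whether one or both do. At the planned rates, about 1 trial in 10 would be positive with only one glue significantly better than control. Ungated pairwise follow-up would carry about 11% familywise error under 50/50/50.

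These sizes rest on two-sided 0.05, 51 evaluable patients per arm, a single final analysis, and the primary read as 14-day closure. That closure rate is listed as a secondary outcome, so the percentages would change under a time-to-event analysis, although the logic would not. The point does not show an arithmetic error or an underpowered trial. It should be corrected, and wording is enough.

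**What to change.** **Statistical analysis section.**

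- Name A vs C and B vs C as the two primary contrasts.
- Keep the three-group test as the gate: test each contrast at two-sided 0.05 only if the three-group test is significant. With three arms this is a closed test, so alpha need not be split between the contrasts. If interim analyses use alpha, the gate is tested at the level available at that analysis.
- Claim efficacy only for a glue whose own contrast is significant in its favour.
- Report A vs B as an estimate with a 95% CI and make no claim that the glues are alike. Label pooled glue vs control as supportive.

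**Sample size section.** State that the 90% power refers to one glue vs control (about 89% with the gate), and that power to show both glues superior is about 84%, at 51 per arm.

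**Cost.** Wording only, with no extra patients or data. The downside is a slightly less favourable power statement.

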#### Outcomes

The primary outcome of the trial is fistula closure time (defined as the interval between the day of enrollment and day of fistula closure) during the 14-day treatment period. Fistula closure is defined as complete closure of the fistula tract and internal and external openings later, which will be confirmed by contrast enhanced computed tomography at each follow-up visit where there is no drainage or any sign of inflammation [17].

In addition to the primary outcome measure of fistula closure, secondary outcomes include closure rates up to 14 days, closure rates up to 180 days, fistula recurrence rates and the incidence of adverse events and severe adverse events up to 180 days (defined as an event that was fatal or life-threatening, led to additional hospitalization or disability or required an intervention to prevent one of these outcomes).

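### The primary outcome is closure time within 14 days, but the named primary test is a Pearson χ² test, which uses neither times nor censoring, and no power is stated for closure time

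*Protocol article*

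**What the plan says.** The Outcomes section states: "The primary outcome of the trial is fistula closure time", counted from enrolment and limited to the 14-day treatment period. The Abstract and the Trial design section agree. The same Outcomes section adds that "secondary outcomes include closure rates up to 14 days", so the proportion closed by day 14 is a separate, secondary measure.

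The Statistical analysis section, under intention to treat, will "examine differences in the fistula closure time among the three groups in the primary analysis by the Pearson" χ² test. After a sentence on safety and secondary efficacy parameters it adds: "Cox proportional hazards models and the Kaplan-Meier method will also be applied". It does not say for which outcome, or whether as a primary or supporting analysis.

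The Sample size section rests on "detecting the minimal, clinically relevant difference in the success rates of the three arms", and "the closure rates in the two treatment groups and one control group are assumed to be 80 % and 50 %, respectively". It arrives at 51 per group for alpha 0.05 and 90% power, then 57 per group and 171 in total after 10% drop-out. It gives no hazard ratio, number of closures or power for closure time.

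**The concern.** Closure time limited to 14 days is a censored time to event. On the plan's own rates, 20% of each glue group and 50% of the control group have no closure time by day 14. With 57 per group that is 57 × 0.2 × 2 + 57 × 0.5 ≈ 51 of 171 patients, or 30%. A Pearson χ² test compares counts in categories. It has no place for a censored time, and it does not use the order of the times.

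If the test is run on closed against not closed by day 14, which the sample size suggests, the confirmatory p-value belongs to an outcome declared secondary. A closure on day 2 then counts the same as one on day 14. A positive result would support a claim about the proportion closed, not about faster closure. With Cox and Kaplan-Meier also available but unranked in an open-label trial, the method could be chosen after the results are known. The Data monitoring section plans an interim analysis on the primary endpoint, so the ambiguity carries into monitoring too.

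**Working it through.** **1. The plan's sample size.** Inputs from the Sample size section: 0.80 against 0.50, alpha 0.05 (sidedness not stated; two-sided taken here), power 90%.

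- Pooled two-proportion formula, mean rate 0.65: n = [1.960 × √(2 × 0.65 × 0.35) + 1.2816 × √(0.8 × 0.2 + 0.5 × 0.5)]² / 0.30² = (1.3221 + 0.8206)² / 0.09 = 51.01, which rounds up to 52. Power at exactly 51 is 89.99%.
- Arcsine formula: 50.7, rounded up to 51.
- Drop-out: 51 / 0.9 = 56.7, so 57 per group; 57 × 3 = 171.

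The stated 51 is therefore reproduced as a pairwise comparison of two closure rates.

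**2. The three-group χ² test on closed or not closed by day 14.** With 80/80/50% the mean rate is 0.70, and the noncentrality is n × (0.1² + 0.1² + 0.2²) / (0.7 × 0.3) = 0.2857n.

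- n = 51: 14.57, power 93.8% (2 df).
- n = 57: 16.29, power 96.0%.

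**3. The log-rank test under proportional hazards.** The documents give no time distribution, so constant hazards are an assumption.

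- HR = ln(1 − 0.8) / ln(1 − 0.5) = 2.32.
- Closures expected with 51 per arm: 51 × (0.8 + 0.5) = 66.3.
- Pairwise power (Schoenfeld), two-sided 5%: Φ(√(66.3/4) × ln 2.32 − 1.96) = Φ(1.47) = 92.9%. Simulation gives 92.2%. With 57 per arm it is 95.2%.
- Closures needed for 90% power: 60 by Schoenfeld (60 / 1.3, about 47 per arm) or 67 by Freedman (67 / 1.3, about 52 per arm).

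**4. Other time patterns.** Pairwise, 51 per arm, day-level times, censored at day 14, by simulation. All timings are assumptions.

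| Assumed pattern | Log-rank | χ² on closed by day 14 |
|---|---|---|
| 80% v 50%, constant hazards | 92% | 90% |
| 80% v 50%, closers in both arms spread evenly over days 1–14 | 85–88% | 88–91% |
| 80% v 50%, control closers all by day 7, glue closers over 14 days | 52% | 90–91% |
| 80% in both arms, glue closers by day 7, control closers over 14 days | 48% | 4% |

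Ranges show the spread over repeated simulations. The last row is the key one: where the arms differ only in speed, the χ² test rejects at about its 5% null level. The three-group version of that row gives 49% and 5%.

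**5. The date of closure.** The Interventions section equates closure with drainage falling to zero and adds tomographic confirmation at follow-up visits. The Outcomes section requires closure of the tract and both openings, confirmed by tomography at those visits. The Participant timeline puts outpatient visits at 1, 3 and 6 months. If those are the visits meant, a closure dated by the scan could not fall inside the 14 days. A time-to-event analysis needs one rule for the date.

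**The case against.** The strongest reply is that the trial foresees a survival analysis and is large enough for one. Much of this stands, and it limits the point in five ways.

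- A reader might infer that closure time is not powered. The documents do not support that. Under proportional hazards with the plan's own rates, 51 per arm gives about 93%. What is missing is any statement or justification of that power.
- A reader might infer that closure time is never analysed. Cox and Kaplan-Meier are named. What they lack is an assigned outcome and primary status.
- A reader might say that a χ² test can only be run on closed against not closed. It could also be run on bands of closure days plus a category for no closure, which keeps some information on speed. The article gives no bands, and its sample size points to the binary version, so that is the likely reading but not the only one.
- A reader might expect the log-rank test to be the more powerful choice throughout. Two of the four assumed patterns above favour the χ² test. The argument is that test and outcome do not match, not that power is sure to rise.
- A pairwise sample size beside a three-group test causes no shortfall (93.8% at 51 per group), and pairwise follow-up tests are commonly left to an analysis plan.

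The Background also credits glue with higher closure rates as well as shorter time, so speed is not its only rationale. None of this removes the contradiction: the article itself assigns the primary analysis of a time to a test that does not use times.

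**Conclusion.** Wrong as written, and it must be corrected. The named primary test does not analyse the declared primary outcome as a time. On the likely reading it tests the 14-day closure rate, which the protocol lists as secondary. Power for closure time is neither stated nor justified.

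The size depends on how glue works. If it raises the 14-day rate from 50% to 80%, either test has reasonable power under constant hazards or even closure, and the harm is mainly to what may be claimed. If it only speeds closure, the χ² test has essentially no power (about 4% against 48% for the log-rank in the assumed example). The mismatch itself rests on the protocol's text alone. The log-rank figures rest on time patterns that the documents do not give.

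**What to change.** Preferred, because it keeps the declared outcome:

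- Make the primary analysis an intention-to-treat log-rank test stratified by the age strata used at randomisation, with censoring at day 14. Report Cox hazard ratios and Kaplan-Meier curves.
- Run the three-group test (2 df) first, then A against C and B against C. With three groups, testing the pairs only after a significant overall test controls the familywise error at 5%.
- Move the χ² test to the secondary 14-day closure rate.
- Reconcile the Interventions and Outcomes sections on which date counts as closure.
- Restate the Sample size section as sized on closure rates. Give pairwise log-rank power at 51 per group as about 93% under assumed proportional hazards (HR 2.32, about 66 closures), with 85–88% and 52% shown for the other assumed patterns.

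The alternative resolves the contradiction equally well: declare 14-day closure the primary outcome, keep the χ² test and the present sample size, and make closure time secondary with log-rank and Cox analyses.

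Either route is a change of wording through a protocol amendment, with no more patients. Drainage is already assessed daily to day 14, so no new data are needed provided the closure date can be set from those records. The change should be made before any interim analysis of the primary endpoint.

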For patients in Group A, autologous PRFG is prepared as described previously [14]. The platelet-rich cryoprecipitate and thrombin are obtained from the whole blood of patients in Group A at least 24 h prior to the start point. Blood collecting packs, prepared with anticoagulant (citrate phosphate dextrose), are used for the collection of whole blood (300 to 400 ml). The platelet-rich plasma (PRP) is separated from the blood by centrifugation at 6 min at 1,000 x*g* twice at ambient temperature. The PRP is transferred to a new pack, and the amount will be determined by weight. From 40 g PRP, equally transferred to two new 300 ml empty packs, the euglobulin fraction is precipitated by dilution with 180 ml citric acid (2.84 mM) in each pack. After thorough mixing, the pack is centrifuged at 3,000 x*g* for 5 min at 4 °C. The supernatant is removed and the precipitate dissolves in 1.625 ml CaCl_2_ (0.1 M). The pH is adjusted by the addition of 1.0 ml NaHCO_3_ (75 mM) in order to initiate the activation of the prothrombin to thrombin [15]. The clot formation is terminated after 30 minutes, and the liquid thrombin solution is removed into microcentrifuge tubes. At the same time, the cryoprecipitate is produced from the rest of the plasma, which is frozen at −80 °C for at least 6 h first and then thawed at 4 °C. After centrifugation at 4,000 rpm/min for 8 min, the cryoprecipitate is harvested by removal of the cryoprecipitate-poor plasma. When applied, fibrinogen and thrombin are thawed at 37 °C from −20 °C until recovery of the liquid state.

Patients in Group B receive glue sealing with commercial sealants. The Porcine Fibrin Sealant Kit (Yueling®, Hangzhou Puji Medical Technology Co. Ltd, Hangzhou, China) is composed of freeze-dried powder of fibrinogen and thrombin and of relevant solutions. Stored at 4 °C, the kit needs to reach room temperature. Then fibrinogen (Component I, > 30 mg/ml) is dissolved by sodium chloride solution (Activator I, 6.0 to 7.0 mg/ml), and thrombin (Component II, 450 to 850 IU/ml) is dissolved by calcium chloride solution (Activator II, 35.0 to 45.0 mg/ml).

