#### Participant timeline

All patients with ECFs in each study site receive SOC, and the fistula output will be evaluated every day. In case of daily output less than 200 ml, the inclusion criteria will be assessed, and imaging examination will be performed to exclude abscesses, obstruction, *etcetera.* Then participants are randomly allocated to Group A (autologous fibrin glue), Group B (commercial fibrin glue) or Group C (drainage cessation). Once enrolled and allocated to Group A, autologous PRFG needs to be prepared. The study period is set as 14 days after the day of enrollment, and fistula drainage will be evaluated every day. All patients are followed up for at least 180 days. The outpatient visits will be scheduled for 1 month, 3 months and 6 months after enrollment (Fig. 1).

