### Data collection, management and analysis

#### Data collection and management

A case report form is used to collect the data for each patient. Assessments are made at the screening period, inclusion (D0) and on days 1 to 14. Assessments include fistula assessment (location, output, duration, and length of fistula tract), monitoring (drainage, catheter, tubes, and adverse events), laboratory tests (hematology, biochemistry, urinalysis, and pregnancy test at inclusion only), and microbiology (blood cultures and cultures of isolates from fistula tracts). Data on adverse events, compliance and concomitant treatments are collected at each visit. Participants will be evaluated every day until the 14th day after randomization. Physicians and research nurses who are not involved in the patients’ care will assess the outcome.

All documents collected in this study will be stored safely in confidential conditions. On all study-specific documents, other than the signed consent, the participant will be referred to by the study participant number/code, not by name. Study documentation will be archived for a period of 5 years after the study.

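### Adverse events are grouped only by randomized arm, so any Group A patient who never receives the glue prepared after allocation dilutes that arm's glue-related harm rate; add a table by treatment received

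*Protocol article*

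**What the plan says.** The Statistical analysis section fixes the grouping for harms: "Adverse events will be tabulated according to randomized group assignment and the proportions will be compared using" Fisher's exact test. Another sentence there covers safety more broadly ("Safety parameters and secondary efficacy parameters will be analyzed using the Pearson" chi-square test, with logistic regression if needed) but names no analysis set. No grouping by treatment received appears anywhere in the article.

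Two sections set the timing in Group A. Participant timeline: "Once enrolled and allocated to Group A, autologous PRFG needs to be prepared". Interventions: the platelet-rich cryoprecipitate and thrombin are "obtained from the whole blood of patients in Group A at least 24 h prior to the start point". The start point is not defined, but allocation must come before the blood draw, and the draw precedes treatment by at least a day. The draw itself is 300 to 400 ml of whole blood. For Group B the same section describes a stored kit brought to room temperature and states no comparable delay.

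Under Outcomes, the safety endpoint is "the incidence of adverse events and severe adverse events up to 180 days". Under Data collection and management: "Data on adverse events, compliance and concomitant treatments are collected at each visit".

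**The concern.** For a superiority claim on efficacy, analysis by allocation is cautious, because patients who miss their treatment pull the arms together. For harms the same pull works the other way: it favours a finding of no difference. Safety is half of the trial's stated objective, and the two glues are different products, so it matters which patients received which.

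The design gives Group A alone a built-in interval between allocation and glue. In that time the draw or the preparation could fail, the patient could withdraw, or the fistula could close. Each such patient still counts in Group A's denominator for glue-related events. If there were enough of them, a reassuring safety result could partly reflect glue that was never given.

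**Working it through.** **The plan's own figures.** The documents give no adverse-event rate and no non-receipt rate, so there is no safety figure to reproduce. The arm size does reproduce. For 80% vs 50% closure, two-sided alpha 0.05 and 90% power, the pooled-variance formula gives 51.01 per group and the arcsine formula 50.75, against the stated 51. Then 51 / 0.90 = 56.7, rounded up to 57, and 3 × 57 = 171. So n = 57 per arm is used below.

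**Assumed inputs, not from the documents.**
- pT, event probability in patients who receive glue: 25%.
- pC, event probability without glue: 5%.
- u, share of Group A never receiving glue: 0, 2%, 10% or 20%. The 10% equals the plan's drop-out allowance, but that allowance is not defined as non-receipt.
- Untreated Group A patients are taken to carry the control risk.

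**Formula.** Group A rate by randomized arm = (1 − u) × pT + u × pC. The difference from control is (1 − u) × (pT − pC), so it shrinks in proportion to u.

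- u = 2%: 0.98 × 25 + 0.02 × 5 = 24.6%
- u = 10%: 0.90 × 25 + 0.10 × 5 = 23.0%
- u = 20%: 0.80 × 25 + 0.20 × 5 = 21.0%

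**Power.** Exact power of the two-sided Fisher test at 0.05, 57 vs 57:

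| Untreated share of Group A | About how many of 57 | Group A rate | Control rate | Difference (points) | Power |
|---|---|---|---|---|---|
| 0 | 0 | 25.0% | 5% | 20.0 | 0.820 |
| 2% | 1 | 24.6% | 5% | 19.6 | 0.806 |
| 10% | 6 | 23.0% | 5% | 18.0 | 0.743 |
| 20% | 11 | 21.0% | 5% | 16.0 | 0.647 |

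**Other assumed rates.** The pattern is the same:

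| Glue vs none | u = 0 | u = 10% | u = 20% |
|---|---|---|---|
| 20% vs 5% | 0.594 | 0.508 | 0.418 |
| 30% vs 10% | 0.705 | 0.615 | 0.518 |

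**Is the loss due to dilution or to fewer patients?** Comparing only the treated Group A patients with 57 controls at 20% vs 5% gives power 0.631 with 51 treated (u = 10%) and 0.605 with 46 treated (u = 20%). Both exceed the diluted 0.508 and 0.418, so dilution is the cause. They also slightly exceed the 0.594 at full receipt. That excess is an artefact of the discreteness of Fisher's test when the arms are equal in size, and should not be read as a gain.

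**The case against.** The strongest reply is that tabulating harms by randomized arm is sound. It is the comparison that randomization protects, and non-receipt is likely to depend on prognosis (early closure, deterioration, unfitness for the draw), so an as-received contrast is confounded. It also charges harms of the 300 to 400 ml draw to Group A, where they belong; a table by glue received alone could lose or misplace them. All of this stands, and it is why the randomized table should be kept.

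It can also be said that an analysis plan not shown may define an exposure-based safety set. That is possible: the article does not exclude one, and its absence from a condensed article would be no finding. The point is narrower. The article does state a grouping for harms, and it is one that can hide non-receipt.

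Third, nothing shows that anyone goes untreated. This too stands: the effect is conditional, and at 2% it is negligible. The assumed rates are illustrative, and the Background reports no treatment-related adverse events in the earlier non-randomized study. Case-level causality assessment of serious adverse events, under Harms, gives some product attribution as well.

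A reader might go further and infer that, because the trial is open-label, controls will also receive glue. At 25% vs 5%, with equal shares crossing over in both directions, power would fall to 0.587 (10%) or 0.335 (20%). The documents do not support this. They offer glue to Groups A and B only, name surgery or conservative care for fistulas unhealed after day 14, and the preparation interval does not cause control crossover. Nor does the interval argument extend to Group B.

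**Conclusion.** The point holds as a limited one. In this document, harms are grouped by randomized arm alone, and Group A's glue exists only after allocation and a blood draw at least 24 h ahead. Any Group A patient who gets no glue therefore moves that arm's glue-related harm rate towards no difference, by a fraction equal to the untreated share. At the assumed 25% vs 5%, power goes from 82% to about 81% with 2% untreated and to 74% with 10%.

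This rests on assumed event rates, an assumed untreated share, and untreated patients having the control risk. If they are untreated because they deteriorated, the dilution would be weaker and could reverse. With full receipt the randomized and as-received groupings coincide.

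It would be too strong to conclude that the randomized tabulation is an error, that it should be replaced, or that the trial will miss a safety difference. The documents support a cheap safeguard and no more.

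**What to change.** In the Statistical analysis section, keep the adverse-event sentence and add, before any results by arm are seen:

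- Adverse events are also tabulated by treatment actually received: autologous glue, commercial glue, no glue.
- The number of patients in each arm who never received the allocated glue is reported, with reasons.
- Group A events after the blood draw but before any glue are shown on a separate line and counted for Group A.
- The as-received table is read beside the randomized table and does not replace it.

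The cost is a few sentences and one extra table. Compliance and concomitant treatment are already recorded at each visit; the one thing to confirm is that the case report form captures the date of first glue application. The drawback is that the as-received contrast is open to confounding, which the text should say. Fixing it in advance matters because, in an open-label trial, a table by treatment received that appears only after the results are known would look selective.
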